## Abstract

**Background:**

Meta-analyses of randomized controlled trials (RCTs) have shown that exercise has beneficial effects on quality of life (QoL) in patients with breast cancer. However, these effects were often small. Blinding in an exercise trial is not possible, which has the possible disadvantage of difficult accrual, drop-out after randomization to control and contamination between study groups (controls adopting the behaviour of the intervention group). The cohort multiple randomized controlled trial (cmRCT) is an alternative for conventional RCTs and has the potential to overcome these disadvantages.

**Methods:**

This cmRCT will be performed within the Utrecht cohort for Multiple BREast cancer intervention studies and Long-term evaLuAtion (UMBRELLA). Patients with breast cancer who visit the radiotherapy department of the University Medical Center Utrecht are asked to participate in UMBRELLA. Patients give consent for collection of medical information, providing patient-reported outcomes through regular questionnaires and randomization into future intervention studies. Patients who fulfill the UMBRELLA Fit study eligibility criteria (12 to 18 months post inclusion in UMBRELLA, low physical activity level) will be randomly allocated to the intervention or control group (1:1 ratio). Patients randomized to the intervention group will be offered a 12-week exercise programme. The control group will not be informed. Regular cohort measurements will be used for outcome assessment. Feasiblity (including participation, contamination, generalizability and retention) of the cmRCT design and effects of the intervention on QoL will be evaluated.

**Discussion:**

We will examine the feasibility of the cmRCT design in exercise-oncology research and compare this with conventional RCTs. Furthermore, the effectiveness of an exercise intervention on the QoL of patients with breast cancer in the short term (6 months) and long term (24 months) will be studied.

**Trial registration:**

Netherlands Trial Register, NTR5482/NL.52062.041.15. Retrospectively registered on 7 December 2015.

**Electronic supplementary material:**

The online version of this article (doi:10.1186/s13063-017-2252-5) contains supplementary material, which is available to authorized users.

## Background

Breast cancer is the most common cancer in women worldwide [1]. In developed countries, more than 85% of women survive for 5 years or longer [2]. As a result, many women live with the consequences of the disease and its treatment. Most patients with breast cancer experience side effects of treatment, including fatigue and impaired quality of life (QoL) [3–6].

Meta-analyses of randomized controlled trials (RCTs) have shown that exercise has beneficial effects on fatigue and QoL in patients with breast cancer [7–10]. Positive effects of physical activity on survival and recurrence have been found in observational research [11]. On the contrary, more sedentary behaviour is associated with higher fatigue levels [12], especially in patients with breast cancer with lower levels of physical activity [13, 14]. Reported exercise effects on fatigue and QoL are often small and this might be partly explained by shortcomings of the RCT design in evaluating exercise interventions that cannot be blinded [15]. The possible disadvantage of not blinding is contamination between study groups, high drop-out after randomization to the control group and difficult accrual [16–18].

The cohort multiple randomized controlled trial (cmRCT) design has been proposed as an alternative to conventional (pragmatic) RCTs [19]. In a cmRCT, the intervention study is performed within a large observational cohort with regular outcome measurements. At cohort entry, two-stage consent is requested for participation in the cohort study and to be randomized for future intervention studies [20]. After randomization, patients who are allocated to the intervention group will be offered the intervention. The control group will not be informed about their role as control in the exercise trial. Outcomes of the intervention group are compared to the outcomes of the control group, using the regular cohort measurements.

### Relative merits of the cmRCT design

The cmRCT design has the potential to overcome some challenges faced in (pragmatic) RCTs studying effects of exercise interventions in patients with cancer. First, in exercise-oncology research, blinding is impossible. As a result, participants allocated to the control group will often also increase their physical activity after randomization [16]. Substantial cross-over of control participants has occurred in over 35% of exercise-oncology RCTs, which might have led to dilution of the intervention effects [16]. Patients with cancer in particular are often motivated to change their lifestyle after diagnosis and, therefore, already intend to increase physical activity levels or attend an exercise programme in the near future [21]. For example, in the Physical Activity during Cancer Treatment (PACT) study, about 50% of the patients with breast cancer randomized to the control group adopted the behaviour of the intervention group [22]. A high level of contamination due to cross-over of controls who adopt the behaviour of the intervention group may decrease the statistical power to detect an intervention effect. Since the control group will not be informed in the cmRCT design about their role as control in the exercise trial, the risk of contamination will be reduced as a result of study participation [23]. Any increase of physical activity levels in the control group now reflects real life and is not caused by participation in an exercise RCT. Furthermore, drop-out in the control group due to disappointment in their allocation will not occur [16, 17].

Previous research has shown that patients with breast cancer who refuse participation in an exercise intervention study are on average older, more fatigued and had more comorbidities than trial participants [18, 24]. Hence, the study population is in general a selective group of younger or less fatigued patients with breast cancer or patients who had less comorbidity after treatment. In addition, higher-educated patients are more willing to participate in health behavior-change interventions [13, 24]. Reasons for the selection may be that trial participation is (unconsciously) not offered to specific subgroups (although fitting the eligibility criteria), that these patients are not willing to participate in an RCT with a 50% chance to be randomized to control or that patients do not want to exercise. Consequently, the generalizability of results will be reduced. Since in a cmRCT design the intervention is offered to eligible patients after randomization and no decisions on being randomized need to be made, participation might be less selective and reflect the real world. As a result, generalizability will increase. However, a prerequisite is that the cohort is representative for the study domain.

Also, long-term effects of physical activity on QoL and fatigue are not clear yet. The cmRCT design is a useful design to study effects in the long term because regular measurements in the prospective cohort will be continued after completion of the exercise intervention trial.

Finally, we expect that recruitment of participants will be easier and faster because patients will be recruited from the cohort. Data obtained by routine measurements can be used to identify eligible patients for the specific trial. Since patients have already signed informed consent to be randomized for future intervention studies, eligible patients allocated to the intervention group can directly be invited by the researchers. Hence, it is not necessary to set up trial recruitment logistics and to recruit a new group of patients with breast cancer.

In addition to the potential benefits, we also expect some challenges. In the cmRCT design, the intervention group is invited for participation after randomization and subsequently do not have to decide about participation in a randomized study. They only need to decide whether they accept or refuse the invitation of an exercise intervention. It might be that due to this approach less motivated patients may also participate, which might result in more drop-out in the intervention group than in the (non-informed) control group. Moreover, more patients with comorbidities might participate in the study compared to conventional RCTs, which also increases the risk of drop-out. Dependent on the amount of drop-out, this will impact the effect estimates from the intention-to-treat analyses [23].

In the UMBRELLA Fit study, the effect of a 12-week supervised exercise intervention on the QoL of patients with breast cancer in the short term and long term will be studied, using the cmRCT design.

## Methods/design

### Aim of this study

The UMBRELLA Fit study follows the cmRCT design (see Additional file 1). Here, patients with breast cancer who participate in the UMBRELLA breast cancer cohort (Utrecht cohort for Multiple BReast cancer intErvention studies and Long-term evaLuAtion) will be randomly selected for a 12-week supervised exercise intervention, 12 or 18 months after enrollment (i.e. postoperatively, prior to consultation of the radiation oncologist) in the UMBRELLA cohort. The purpose of the UMBRELLA Fit study is twofold. The first aim is to assess the feasibility and therefore, we will (1) assess the participation rate and intervention compliance in the intervention group and drop-out rates in the intervention and control group; (2) compare the (change in) physical activity levels in the intervention and control group during the intervention period; and (3) assess whether a more diverse generalizable study population will be included by comparing characteristics of the included study population with characteristics of patients participating in previous breast cancer exercise trials with a conventional RCT design. Our second goal is to examine the effectiveness of the exercise intervention on the QoL of patients with breast cancer in the short term (6 months) and long term (24 months).

### Patients

We will make use of the UMBRELLA cohort, which aims to generate short-term and long-term data on clinical and patient-reported outcomes during and after breast cancer treatment and to provide infrastructure for multiple randomized evaluations of the intervention in patients with breast cancer [25]. Recruitment started in September 2013 at the University Medical Centre (UMC) Utrecht and all patients with breast cancer who are referred to the department of radiation oncology of the UMC Utrecht for radiation treatment are asked to participate in the UMBRELLA (see Figs. 1 and 2) [25]. They give consent for the use of routinely collected clinical data and prospective collection of patient-reported outcome measures through regular questionnaires. In addition, they can opt to give consent to be randomized for future intervention studies within the cohort. Patients will be informed that they will be offered an experimental intervention if they are randomly selected for the intervention group. They are also informed that they will not be contacted when randomly selected for the control group and that their data can be used in a trial context [20]. Between the start of recruitment and July 2016, 88% of the eligible patients who were invited for participation in UMBRELLA gave consent to participate and 87% of those who agreed to participate also consented to be randomized for future intervention studies within the cohort [25].

**Fig. 1 Fig1:**
[figure not shown]
The cohort multiple randomized controlled trial (cmRCT) design (adapted from Relton et al.)

**Fig. 2 Fig2:**
[figure not shown]
Standard Protocol Items for Intervention Trials (SPIRIT): schedule of enrollment, interventions and assessments

For the UMBRELLA Fit study, participants in UMBRELLA who meet the following criteria are eligible: (1) UMBRELLA informed consent for randomization to future intervention studies; (2) 18–75 years of age; (3) 12 months or 18 months after enrollment in the UMBRELLA cohort, (4) primary cancer treatment completed (except for adjuvant hormonal treatment); and (5) a physically inactive lifestyle (less than 150 min/week performing moderate to vigorous leisure time and sports activities, ≥ 4 metabolic equivalent (MET)) as measured by the Short QUestionnaire to ASsess Health-enhancing physical activity (SQUASH) [26]. Patients with a contra-indication (e.g. neurological problems, arrhythmias and walking problems) to exercise will be excluded.

### Recruitment and allocation

UMBRELLA participants meeting the inclusion criteria will be randomly allocated to the intervention or control group with a 1:1 ratio, by an independent data manager using a computer-generated randomization list. Randomization will be stratified for time since enrollment (12 or 18 months). Patients randomized to the intervention group will receive an offer by mail to participate in an exercise programme, a patient information sheet and an informed consent form. After 1–2 weeks these patients are contacted by telephone to further explain the study. If patients decide to participate, a last check of eligibility will be performed. Contra-indications to the exercise programme will be screened using the Physical Activity Readiness Questionnaire (PAR-Q) [27]. If eligible, they will be invited to visit the UMC Utrecht to sign the informed consent form for the UMBRELLA Fit study and undertake a baseline assessment. If patients refuse to participate because of bad timing of the invitation, they will be asked if they are willing to start later. Patients randomized to the control group will not be informed about the study. Recruitment started in October 2015.

### Exercise intervention

The exercise intervention is a 12-week structured exercise programme. Patients are offered two one-hour supervised fitness group or individual sessions per week at a physiotherapist centre close to the patient’s home. The training programme is a combination of moderate to high-intensity aerobic training and strength training. Sessions include a 5-minute warm up, aerobic and strength training (50 minutes) and a cool down.

The programme will be tailored to the patient’s physical fitness level. The intensity of aerobic training is determined by the heart rate reserve, based on the guidelines of the American College of Sports Medicine [28]. Patients’ individualized target heart rate zones during aerobic training are based on the results of a cardiopulmonary exercise test which is performed at baseline. Target hearts rates are calculated by the formula:$$ \mathrm{Target}\kern0.17em \mathrm{heart}\kern0.17em \mathrm{rate}=\mathrm{resting}\kern0.17em \mathrm{heart}\kern0.17em \mathrm{rate}+\left[\mathrm{intensity}{\left(\%\right)}^{\ast}\left(\mathrm{maximal}\kern0.17em \mathrm{heart}\kern0.17em \mathrm{rate}-\mathrm{resting}\kern0.17em \mathrm{heart}\kern0.17em \mathrm{rate}\right)\right] $$

Aerobic training will be performed on an exercise machine (e.g. a treadmill, exercise bike, crosstrainer), depending on the patient’s preference. The intensity and duration of the aerobic training will be gradually increased (Table 1).

**Table 1 Tab1:** Overview of the exercise programme

Week	Aerobic training	Strength training
1–3	15–20 min 40–60% HRR + HR_rest_	1 set of 20–25 repetitions (20 RM test) of 9 exercises: row (back), chest press (chest), squat (legs), shoulder press (shoulders), bicep curl (biceps), lunges (legs), calf raises (calves), tricep extension (triceps), crunch (abdominals, 20–40 repetitions)
4–8	15–20 min 60–70% HRR + HR_rest_ 5–10 min 70–89% HRR + HR_rest_	2 sets of 15–20 repetitions (15 RM test) of 7 exercises: row (back), chest press (chest), squat (legs, 20–25 repetitions), shoulder press (shoulders, 10–15 repetitions), bicep curl (biceps), tricep extension (triceps), crunch or hoover (abdominals, 30–50 repetitions or seconds)
9–12	10 min 60–75% HRR + HR_rest_ Interval training: 10 × 30 sec, 1 min active rest between each interval	

*HRR*: heart rate reserve, *HR*
_*rest*_: resting heart rate

HRR = maximal heart rate - resting heart rate

Strength training consists of a set of exercises, focusing on all major muscle groups. During the intake session at the physiotherapist centre, 20 repetition maximum (RM) tests will be performed to determine the training load (the maximum weight at which a muscle group can perform 20 repetitions) for the different exercises. These weights will be the starting point for each strength exercise. A 20 RM and 15 RM test will be repeated in the fourth and eight weeks of the programme (Table 1). In the case of physical limitations, the exercise programme will be adapted in consultation with the researchers.

In addition to the supervised exercise programme, patients will be stimulated to develop an active lifestyle. An active lifestyle is defined as being moderate to highly physically active for at least 30 min a day, according to the World Cancer Research Fund/AICR, American Institute for Cancer Research (WCRF/AICR) guidelines for patients with cancer (www.aicr.org). If necessary, in consideration with the physiotherapist, patients will gradually increase their physical activity level during the first four weeks of the programme until they adhere to the WCRF/AICR guideline.

Patients will also be encouraged to reduce sedentary time during the day. Patients will receive a wristband, the Jawbone UP2™ (Jawbone, San Francisco, CA, USA), to track activity and raise awareness of their sedentary behaviour. The “Idle” alert will be used, i.e. the band gently vibrates when the patient has been inactive for a period of 45 minutes. Furthermore, the activity tracker and the accompanying Smart Coach application will be used to encourage an active lifestyle by, amongst others, setting personal step-goals per day and giving personalized feedback on patients’ activity levels.

To enhance adherence to the exercise programme and help patients to achieve and maintain an active lifestyle, physiotherapists are instructed to motivate patients according to the principles of Bandura’s social cognitive theory (SCT), i.e. enhancing self-efficacy by giving positive feedback on their progress and the starting point of the training schedule has been carefully chosen so it will be likely that the patient will succeed [29]. As a result, it is expected that patients develop a feeling of mastery (mastery experience).

### Control group

Control patients are not aware of study participation and will receive usual care. After completion of the UMBRELLA Fit study, all UMBRELLA participants, irrespective of participation in this study, will be informed by the annual newsletter.

### Endpoints

#### Methodological endpoints

##### Acceptance of the intervention

Acceptance of the intervention is defined as the percentage of patients who are randomized to the exercise intervention and accept participation.

##### Physical activity behaviour

To gain insight into the contrast between physical activity levels, changes in physical activity level in the control group will be described and compared to changes in the intervention group. Since the control group is not aware of study participation, a possible increase in physical activity level in the control group (contamination) is not the result of study participation but may be explained by real-life factors, e.g. motivation to change their lifestyle after diagnosis. Physical activity level will be evaluated in regular cohort measurements using the SQUASH [26]. This questionnaire contains questions on commuting activities, leisure-time and sports activities, household activities and activities at work. It consists of three main queries: days per week, average time per day and intensity.

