#### Effectiveness endpoints

We will use the regular questionnaire measurements of the UMBRELLA cohort to assess QoL, fatigue, anxiety and depression, and sedentary behaviour. Patients are included 12 or 18 months after enrollment in the UMBRELLA cohort. The most recent questionnaires filled in before enrollment in the UMBRELLA Fit study will serve as baseline measurements. Questionnaires 6 and 24 months later will be used as follow-up measurements.

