Another challenge is the dependence on information collected within the cohort for the assessment of eligibility and for the outcome. If the available information is insufficient, there is a possibility that selected participants will not meet the inclusion criteria, e.g. due to severe comorbidity not yet registered in the cohort. However, since randomization has already been executed, these patients stay in the intention-to-treat analyses. In addition, another limitation of dependency on routine measurement outcomes is that the potential cmRCT outcomes are limited to outcome measures already collected in the observational cohort study. There is no opportunity to obtain additional information from the control group by additional measurements or at additional time points.

Patients are enrolled at 12 or 18 months after inclusion in UMBRELLA because at this time most of these patients have finished their primary treatment. In this period, the impact of diagnosis and treatment on normal daily living (e.g. complaints of fatigue, impaired quality of life) become more prominent [3–6]. Because previous research has shown that exercise has a beneficial effect on the QoL of patients with breast cancer in this period, the UMBRELLA Fit study gives the opportunity to assess the feasibility of the cmRCT design in the field of exercise-oncology by comparing the results of this trial with previous exercise trials in patients with breast cancer.

In summary, the UMBRELLA Fit study examines the effects of exercise on the QoL of patients with breast cancer, using the cmRCT design. The purpose of this study is twofold. The first goal is to determine the feasibility of the cmRCT design in the field of exercise-oncology and compare this with conventional RCTs in this field. The second goal is to examine the effectiveness of the exercise intervention on the QoL of patients with breast cancer in the short term (6 months) and long term (24 months).

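### A rise in control-arm activity from the pre-enrolment SQUASH may be partly regression to the mean, so reading it as contamination may overstate contamination

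*Protocol article*

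**What the plan says.** All references are to the protocol article.

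- **Entry (Patients, eligibility criteria).** One criterion is "a physically inactive lifestyle (less than 150 min/week performing moderate to vigorous leisure time and sports activities", at 4 MET or more, as measured by SQUASH.
- **Outcome (Physical activity behaviour).** "Physical activity level will be evaluated in regular cohort measurements using the SQUASH". Control-arm changes are to be described, and also compared with changes in the intervention arm.
- **Baseline (Effectiveness endpoints).** "The most recent questionnaires filled in before enrollment in the UMBRELLA Fit study will serve as baseline measurements". This is written for quality of life, fatigue, anxiety and depression, and sedentary behaviour. The Discussion rules out any extra control measurement: "There is no opportunity to obtain additional information from the control group by additional measurements or at additional time points".
- **Interpretation.** Physical activity behaviour says that "a possible increase in physical activity level in the control group (contamination) is not the result of study participation", and adds, with a hedge, that real-life factors may account for it. Relative merits of the cmRCT design has no such hedge: "Any increase of physical activity levels in the control group now reflects real life".
- **Analysis (Methodological outcomes).** Activity change is compared between arms by ANCOVA or a mixed model adjusted for baseline.

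Regression to the mean is not mentioned.

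**The concern.** The questionnaire that makes a patient eligible by being low also appears to be the starting point for measuring her change. Some of those low scores are low through reporting error or an untypical week. At the next questionnaire such scores tend to move back up, so the group mean rises with no shift in the cohort's activity. The article leaves no room for this explanation.

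What is at stake is the first aim of the study. The abstract lists contamination among the feasibility components, and the Discussion promises a comparison with conventional trials. The Background figures are control-arm figures: about 50% of controls adopting the intervention behaviour in one earlier exercise trial, and substantial cross-over in over 35% of exercise-oncology trials. A control rise that is partly artefact would make the cohort design look more contaminated than it is, or would be put down to lifestyle motivation that did not occur.

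**Working it through.** **The plan's own figure.** There is none for activity change or contamination. The quality-of-life sample size (98, then 83 per group) does not depend on this point.

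**Inputs.** From the article: threshold c = 150 min/week, the same instrument at entry and follow-up, 1:1 randomisation after the entry rule. Assumed, because the article does not give them: the SQUASH distribution in the cohort and the correlation r between successive questionnaires. The 0.4 in the sample-size section is for quality of life and cannot stand in for r.

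**Log-normal model, no change in the cohort distribution.** With median m and log-SD s, let a = ln(c/m)/s. For patients whose first score is below c:

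- mean at entry = m·exp(s²/2)·Φ(a − s)/Φ(a)
- mean at follow-up = m·exp(s²/2)·Φ(a − r·s)/Φ(a)
- share at or above c at follow-up = 1 − Φ₂(a, a; r)/Φ(a), where Φ₂ is the bivariate normal distribution function

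*Example:* m = 120, s = 0.8, r = 0.65.

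- a = ln(1.25)/0.8 = 0.279, Φ(a) = 0.610, m·exp(0.32) = 165.3
- entry mean = 165.3 × 0.301/0.610 ≈ 82 min/week
- follow-up mean = 165.3 × 0.405/0.610 ≈ 110 min/week
- apparent rise about 28 min/week; 22% at or above 150

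| Median | log-SD | r | Entry mean | Follow-up mean | Rise | At or above 150 |
|---|---|---|---|---|---|---|
| 90 | 0.8 | 0.8 | 73 | 84 | 11 | 11% |
| 120 | 0.8 | 0.65 | 82 | 110 | 28 | 22% |
| 150 | 1.0 | 0.5 | 78 | 153 | 74 | 33% |

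The first and last rows are the ends of the range for medians 90 to 150, log-SD 0.8 to 1.0 and r 0.5 to 0.8. At r = 0.9, over the same medians and log-SDs, the rise is 5 to 13 min/week and 8 to 14% cross.

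**Normal model as a cross-check.** Rise = (1 − r)·SD·φ(a)/Φ(a), with a = (150 − mean)/SD. For mean 150 and SD 100, φ/Φ = 0.798, so r = 0.7 gives 0.3 × 100 × 0.798 = 24 min/week. For mean 200 and SD 150, φ/Φ = 1.021, so r = 0.7 gives 0.3 × 150 × 1.021 = 46. At r = 1 the rise is 0.

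**Between-arm contrast.** Simulated trials of 166 patients (2 × 83), assumed mean 200, SD 150 and r = 0.6, entry below 150, 4,000 runs. With no true effect both arms rise by about 61 min/week, the ANCOVA contrast is 0.2 and the rejection rate at the 5% level is 4.7%. With a true effect of 40 the contrast is 40.5. The artefact is equal in both arms and cancels.

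**The case against.** The case against is substantial, and most of it limits the point rather than removing it.

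- *The key sentence is not false.* Regression to the mean is not a result of study participation either, and the real-life explanation there is hedged. This stands. The unhedged wording is in the Background. Still, neither section allows for an explanation other than real change.
- *The formal analysis is immune.* This stands. A reader might infer that the planned activity comparison is biased; it is not. But the contrast combines the intervention effect with the control change, so it cannot show how much controls changed. The article also plans to describe that change.
- *No contamination rate is defined.* This stands. The article sets no cut-off for controls and no formal comparison with the 50% figure. Methodological outcomes names participation, compliance, retention and drop-out for comparison with other trials. The share crossing 150 min/week illustrates size and is not a planned endpoint.
- *The premises are partly inferred.* The baseline sentence does not name physical activity, and the article does not say that one questionnaire alone decides eligibility. With no extra control measurements possible, however, the qualifying or nearest earlier questionnaire is the likely starting point. Entry uses only leisure and sports activity at 4 MET or more, whereas SQUASH also covers commuting, household and work; if the total is analysed, the effect is weaker.
- *An article leaves caveats to the full protocol.* True of omissions. Here the article states an interpretation, and in the Background states it without qualification.

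**Conclusion.** The point holds in a limited form. The described within-control rise may be partly regression to the mean, and taking it as contamination may overstate contamination. The direction is known whenever the correlation between successive scores is below 1 and change is measured from the qualifying score. The size is not: about 11 to 74 min/week and 11 to 33% crossing the threshold under the log-normal assumptions, less with a more reliable measure or a broader activity total.

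A reader might go further and conclude that the feasibility result on contamination is definitely overstated. The documents do not support that: they define no such result numerically and give no SQUASH reliability or spread. The between-arm activity contrast and the quality-of-life analysis are not put in doubt by this point.

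**What to change.** 1. Amend Relative merits of the cmRCT design and Physical activity behaviour so that a control-arm rise from the pre-enrolment questionnaire is not in itself read as contamination or real-life change, and name regression to the mean as an alternative explanation.
2. Rest the conclusion about contrast in activity on the baseline-adjusted between-arm comparison already planned.
3. Report the control change beside the rise expected from regression to the mean. Estimate that rise from repeated SQUASH scores of all cohort members, active and inactive, at the same time points, for the same activity variable. Exclude those offered the intervention, and weight the remaining eligible members so that inactive patients are not under-represented.
4. Use that benchmark in any comparison of contamination with conventional trials.

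Do not measure change in the 18-month stratum from the month-12 score, although this looks like a simple way round the selection. Patients inactive at month 12 could have been randomised then, so 18-month entrants may be selected for having been active at month 12. In the example above (median 120, log-SD 0.8, r 0.65, no true change), patients at or above 150 at month 12 and below it at month 18 go from a mean of 232 at month 12 to 167 at follow-up if all pairs of scores are equally correlated, or 129 if correlation decays with time. That is a spurious fall of 65 or 103 min/week. The real mix of entrants is unknown.

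The cost is a change of wording and a small extra analysis of data the cohort already collects. The expected-rise benchmark assumes that the cohort's activity distribution is stable between the time points, and this should be stated with the result.
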